# Effect of consuming food cooked in iron pots and behavior change communication on iron status in non-pregnant, non-lactating women: protocol for randomized controlled trial

**DOI:** 10.1186/s13063-025-09202-0

**Published:** 2025-10-31

**Keywords:** Anemia, Iron-deficiency, Randomized controlled trials as topic, Cooking, Iron, Dietary, Hemoglobin, Ferritin, Patient compliance, Rural population

## Abstract

**Background:**

Iron-deficiency anemia (IDA) remains a significant public health concern, particularly among women of reproductive age in developing countries. Despite ongoing supplementation and fortification programs, the prevalence of anemia remains high due to challenges such as poor compliance, logistical constraints, and limited access to iron and dietary sources. Cooking in iron cookware has been proposed as a low-cost, culturally acceptable strategy for improving dietary iron intake; however, evidence of its effectiveness remains mixed. This randomized controlled trial (RCT) aimed to evaluate the effectiveness of consuming food cooked in iron pots, coupled with a structured behaviour change programme, on improving hemoglobin and ferritin levels among non-pregnant, non-lactating women of reproductive age in rural India.

**Methods:**

A community-based randomized controlled trial will be conducted in selected rural blocks of Akola and Wardha districts in Maharashtra, India. Eligible women (aged 18–45 years, non-pregnant, non-lactating) will be randomized into two groups: an intervention group receiving iron cookware along with structured behaviour change communication sessions, and a control group receiving non-iron cookware. Iron status indicators (hemoglobin, ferritin, serum iron, transferrin saturation, and total iron-binding capacity) will be assessed at baseline, 6 months, and 12 months after the intervention. Patient compliance with iron pot usage will be monitored through food diaries, spot checks, and interviews. Barriers and facilitators of adherence will be explored through qualitative assessments.

**Discussion:**

It is anticipated that women using iron cookware with structured counselling support will demonstrate significant improvements in anemia and iron deficiency indicators compared to controls. This study will also identify the practical, cultural, and economic barriers affecting patient compliance with cooking in iron pots. The findings will contribute to the evidence base for promoting iron cookware as a sustainable intervention in rural population settings. The results will inform community health strategies and align with India’s Anemia Mukt Bharat initiative.

**Trial registration:**

This randomized controlled trial was prospectively registered with the Clinical Trials Registry–India (CTRI) under the registration number CTRI/2025/04/085829, dated April 28, 2025.

**Supplementary Information:**

The online version contains supplementary material available at 10.1186/s13063-025-09202-0.

Role of trial sponsor and funders in design, conduct, analysis, and reporting of trial; including any authority over these activities {3c}	This is an investigator-initiated trial. The sponsor (Government Medical College, Akola) and co-affiliated institute (DMIMS Wardha) had no role in the study design, data collection, management, analysis, interpretation, report writing, or decision to publish. The investigators assume full responsibility for the study.
Composition, roles, and responsibilities of the coordinating site, steering committee, endpoint adjudication committee, data management team, and other individuals or groups overseeing the trial, if applicable{5d}	Coordinating Center: Department of Community Medicine, Government Medical College (GMC), Akola. Overall coordination of the trial, field operations, recruitment, follow-up, data entry, and communication between the investigators. Steering Committee: Principal Investigator ([name]), Co-Investigators ([name], [name] [name], [name], [name] [name], [name]), Senior Mentor ([name]) provides strategic oversight, ensures adherence to the protocol, monitors progress, reviews interim findings, and addresses operational challenges. Data Management Team: GMC Akola (data entry staff and statistician) and DMIMS Wardha (epidemiology and biostatistics experts) are responsible for data entry, cleaning, validation, and secure storage. Oversees database creation and quality checks and ensures the confidentiality of participants’ data. Endpoint Adjudication Committee: Not applicable (endpoints are objective laboratory measures: hemoglobin, ferritin, iron indices) : N/A Data Monitoring Committee (DMC): Not constituted (minimal risk, non-drug, behavioural/nutritional trial) Safety monitoring incorporated into Steering Committee meetings; ethical oversight through Institutional Ethics Committees (IEC) at GMC Akola and DMIMS Wardha. Ethics Oversight: Institutional Ethics Committee (IEC), Government Medical College Akola; Institutional Ethics Committee, Responsible for initial and continuing ethical approval, monitoring compliance with national/international ethical standards, and reviewing any protocol amendments.
Name of trial registry, identifying number (with URL), and date of registration. If not yet registered, name of intended registry (4)	This randomized controlled trial is prospectively registered with the Clinical Trials Registry - India (CTRI) under registration number CTRI/2025/04/085829, dated 28 April 2025. URL: https://ctri.nic.in/Clinicaltrials/pubview2.php
Where the trial protocol and statistical analysis plan can be accessed (5)	The full trial protocol and Statistical Analysis Plan (SAP) will be made available as supplementary files in the publication of the protocol in *Trials* and deposited in an institutional repository (Government Medical College Akola website) and Shod Ganga (URL:https://shodhganga.inflibnet.ac.in/) with open access.
Where and how the individual de-identified participant data (including data dictionary), statistical code, and any other materials will be accessible (6)	De-identified individual participant data (IPD), data dictionary, and statistical code will be made available in an open data repository (Dryad) within 6 months of primary outcome publication. Requests may also be directed to the PI (e-mail).
Sources of funding and other support (e.g., supply of drugs) (7a)	This study is supported by the Datta Meghe Institute of Higher Education & Research (DMIHER) and Government Medical College Akola, Maharashtra. No commercial entity influenced the study design or reporting.
Financial and other conflicts of interest for principal investigators and steering committee members (7b)	The investigators declare no financial or non-financial competing interests related to this study.
Plans to communicate trial results to participants, healthcare professionals, the public, and other relevant groups (e.g., reporting in trial registry, plain language summary, publication) (8)	The results will be communicated to participants (via community meetings and leaflets in the local language), healthcare professionals (through CME/workshops), the public (press releases, social media), and the scientific community (trial registry updates, peer-reviewed publications, conference presentations). A plain-language summary will be uploaded to the trial registry.

## Introduction

### Background and rationale {9a &9b}

Iron deficiency anemia (IDA) remains a critical public health issue, particularly in developing countries such as India. It disproportionately affects women of reproductive age, children, and other vulnerable populations, leading to impaired cognitive and physical development, reduced productivity, and an increased risk of adverse maternal and neonatal outcomes. Despite the implementation of iron supplementation and fortification programs, the prevalence of anemia remains persistently high, as reported by national surveys such as the National Family Health Survey (NFHS) [1–3]. According to the World Health Organization, globally, approximately 30% of non-pregnant women of reproductive age (15–49 years) suffer from anemia. In India, the prevalence of anemia among non-pregnant, non-lactating women in this age group is approximately 57%, according to the NFHS-5 (2019–21), indicating a severe public health concern [1].

Iron supplementation is widely used to combat anemia; however, its effectiveness as a standalone intervention is often limited by factors such as cost, logistical challenges, poor adherence, and side effects like nausea, vomiting, and constipation. Although fortification of staple foods is cost-effective, it faces similar obstacles, including regulatory constraints and consumer acceptance issues [4]. While biofortification through agricultural innovations holds promise, its impact on key outcomes, such as hemoglobin levels in children, remains uncertain [5]. Dietary diversification is another potential approach; however, access to iron-rich foods, such as meat, and vitamin C-rich produce is often restricted in low-income populations. Additionally, common dietary staples, including cereals, coffee, and tea, contain iron absorption inhibitors, further complicating anemia management [6]. Addressing infections like malaria and intestinal parasites is also crucial, yet these efforts must be integrated within broader nutritional strategies due to the multifaceted nature of anemia [7] Given the persistent burden of IDA, innovative, culturally appropriate, and sustainable interventions are needed. One such strategy is the use of iron cookware, which has gained attention for its low cost, cultural acceptability, and potential to increase dietary iron intake [8]. Cooking in iron pots allows iron to leach into food, potentially enhancing iron consumption, which is an especially relevant intervention in low-resource settings where access to fortified foods or supplements is inconsistent. However, the effectiveness of iron cookware remains inconclusive, as existing studies have reported mixed results. The amount and bioavailability of leached iron depend on several factors, including food acidity, cooking time, and cookware condition [9]. Additionally, cultural practices and user compliance significantly influence the sustained use of these technologies. While some studies have demonstrated modest improvements in hemoglobin levels, others have shown minimal or no impact, highlighting the need for more rigorous, context-specific research [10]

Furthermore, several key variables influencing the efficacy of iron cookware remain unexplored. These include genetic hemoglobinopathies (e.g., thalassemia traits), water quality, and the potential risk of iron overload in certain populations [11]. Most previous studies on iron cookware have focused on children or pregnant women, while non-pregnant, non-lactating women (NPNL) who face a high burden of anaemia remain understudied [8]. In Indian households, this group is usually responsible for daily cooking, making them the most strategic targets for an intervention that uses iron cookware. Importantly, by engaging NPNL women through structured behavior change communication (BCC), this trial not only empowers them but may also indirectly improve iron intake and stores among other family members who consume meals prepared in iron pots [12]. Compliance with the consistent use of iron pots and the practicality of integrating them into daily cooking habits are critical factors that require further investigation. Without addressing these gaps, it is difficult to determine the true public health impact of iron cookware. Therefore, the present study aimed to evaluate the sustained use of iron pots in women of reproductive age, examining their impact on dietary iron intake and biomarkers.

### Objectives {10}

To evaluate the impact of consuming food cooked in iron pots on iron status indicators, specifically hemoglobin (Hb), serum ferritin, serum iron, transferrin saturation (TSAT), and total iron binding capacity (TIBC) in non-pregnant, non-lactating women of reproductive age group from rural IndiaTo assess the effect of cooking in iron pots on erythrocyte protoporphyrin, mean corpuscular volume, and C-reactive protein as markers of iron metabolism and inflammationTo evaluate the compliance rates of Indian households in using iron cookware consistently for meal preparation.To identify the practical, cultural, and economic barriers impacting the consistent use of iron cookware in Indian households.

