### Trial design {12}

This is a two-arm, parallel-group, superiority, randomized controlled trial with an allocation ratio of 1:1. Participants will be randomized to receive either iron cookware for daily food preparation plus behaviour change communication package (intervention group) or standard care (control group). Control Group participants will use their usual utensils (such as aluminium or stainless steel) for daily food preparation.

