### Health education and behaviour change communication (BCC) sessions

The effectiveness of cooking with iron utensils will be evaluated alongside behaviour change communication (BCC) strategies, ensuring that participants adopt and sustain cooking practices that optimize iron absorption. To reinforce knowledge and promote long-term adherence, the study team will conduct group sessions and household visits, focusing on the role of dietary iron, i.e., understanding iron-rich food sources, factors that enhance absorption (e.g., vitamin C), and dietary inhibitors (e.g., tea, coffee, phytates); Anemia Prevention and Management which includes raising awareness about the consequences of iron deficiency and the importance of routine hemoglobin checks and Sustained Behaviour Change for encouraging the habitual use of iron cookware through community-driven approaches, including storytelling and role modelling by early adopters.

Participants in the intervention group will receive fortnightly group BCC sessions for the first 3 months, followed by monthly group sessions for the next 3 months (total, 9 group sessions over 6 months). In addition, monthly individual home visit sessions will be conducted throughout the 6-month intervention period to reinforce key messages, address practical barriers, monitor cookware usage, and offer personalized support. Each group session will last approximately 45–60 min, while home visits will be of 20–30 min duration, ensuring context-specific engagement and continuous motivation.

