### How blinding will be achieved {24b}

To maintain blinding, all blood samples will be labelled with anonymized study codes rather than allocation labels. Therefore, the laboratory staff will be unaware of the participants’ group assignments. Similarly, the trial statistician will receive only coded datasets where groups are labelled “Group A” and “Group B.” The cookware used in the intervention arm differed visibly from the control cookware (iron vs. non-iron); hence, participant blinding was not feasible.

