This study anticipates generating new knowledge on the effectiveness of iron cookware in improving iron status across diverse demographic groups in Indian households. By evaluating changes in hemoglobin and iron biomarkers, it will provide evidence on the bioavailability of iron leached during cooking [9]. The research will also identify compliance rates, user acceptability, and practical barriers, offering insights into cultural and behavioural factors influencing cookware adoption. Additionally, the findings will contribute to public health strategies by comparing the intervention with existing anemia prevention measures, ultimately providing actionable recommendations for addressing iron deficiency anemia in resource-limited settings [8, 9].

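### Objectives 1 and 2 and the leached-iron claim credit iron pots alone, but the two arms compare pots plus counselling with a control condition that the article describes in two ways

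*Protocol article*

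**What the plan says.** Objectives {10} opens with "To evaluate the impact of consuming food cooked in iron pots on iron status indicators". The second objective is framed the same way for protoporphyrin, MCV and CRP. Neither names BCC.

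Trial design {12} states "This is a two-arm, parallel-group, superiority, randomized controlled trial with an allocation ratio of 1:1". The intervention group gets iron cookware plus a BCC package and the control group gets standard care. No pots-only or BCC-only arm is described.

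The section on health education and BCC sessions gives the intervention group 9 group sessions over 6 months plus monthly individual home visits. The content includes "understanding iron-rich food sources, factors that enhance absorption (e.g., vitamin C), and dietary inhibitors (e.g., tea, coffee, phytates".

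The Discussion says that "it will provide evidence on the bioavailability of iron leached during cooking" and that the findings will contribute by "comparing the intervention with existing anemia prevention measures". It also sets out to establish iron cookware, without mention of BCC in that sentence, as a scalable strategy.

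On the comparator, the Abstract (Methods) describes "a control group receiving non-iron cookware". Trial design {12} says "Control Group participants will use their usual utensils (such as aluminium or stainless steel) for daily food preparation". The blinding section {24b} says that the intervention cookware "differed visibly from the control cookware (iron vs. non-iron").

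**The concern.** A two-arm trial estimates one contrast. Here that contrast is cookware, dietary teaching and any additional contact taken together. If diet advice alone improved ferritin or haemoglobin, the result would meet Objective 1 as worded and could be cited as evidence that iron leached from pots is absorbed, although the design could not have shown this. The results are meant to inform national anaemia programmes, where distributing cookware and running a counselling programme are different decisions.

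The comparator conflict is a separate defect. Whether controls are handed a new non-iron set or keep what they own changes the contrast. The exclusion criteria remove only women who already use iron cookware regularly, so occasional users may enter, and a supplied set could displace that use. It also changes the control-arm cost in the exploratory cost-effectiveness ratio.

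**Working it through.** **1. What differs between the arms**

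| Component | Intervention | Control | Source |
|---|---|---|---|
| Iron cookware set | supplied | no | {12}, {15} |
| Teaching on iron sources, enhancers, inhibitors | yes | none described | BCC sessions |
| Group BCC sessions | 9 | none described | BCC sessions |
| Monthly BCC home visits, 6 months | yes | not described; visits elsewhere name no arm | BCC sessions; {15c}, {17}, {25b} |
| Non-iron cookware | – | supplied, or own utensils | Abstract; {12} |

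Group sessions: fortnightly for 3 months = 6, plus monthly for 3 months = 3, total 9, as the article states. Home visits: 6 months × 1 = 6. Time: 9 × 45 min + 6 × 20 min = 525 min = 8.75 h at the low end, and 9 × 60 + 6 × 30 = 720 min = 12 h at the high end. This is the BCC described for the intervention group. It is not a between-arm difference in all contacts.

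**2. The sample size reproduces and is not the problem**

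Inputs from Sample size {19}: Δ = 0.5 g/dL, SD = 1.2 g/dL, two-sided α = 0.05, power 80%, attrition 10%.

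n per arm = 2 × [SD × (1.960 + 0.842) / Δ]² = 90.42, so 91. With attrition, 90.42 / 0.9 = 100.5, so 101 per arm and 202 in total, as stated. Rounding to 91 before inflating gives 102 per arm (204). The arithmetic is sound for the package contrast.

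**3. What a significant result would say about pots**

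The article does not split the 0.5 g/dL between pots and BCC, so the following is an assumed range. Suppose that the pots have no effect and BCC alone raises haemoglobin by b. With 91 evaluable per arm, the standard error is 1.2 × √(2/91) = 0.178, and the probability of significance is about Φ(b/0.178 − 1.96):

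| b (g/dL, assumed) | Probability of significance |
|---|---|
| 0.2 | 20% |
| 0.3 | 39% |
| 0.4 | 61% |
| 0.5 | 80% |

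The last row equals the planned power. The test responds identically whether the 0.5 g/dL comes from pots, from BCC or from both, so significance cannot tell them apart.

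**4. Do the planned analyses separate them?**

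Additional analyses {27d} lists adjustment for dietary intake. Diet measured after baseline is itself a target of BCC, so adjusting for it conditions on a consequence of the intervention. The per-protocol analysis in {27b} selects on cookware adherence, which is not randomised, and compliant women have also been offered the BCC. Neither gives a randomised pots-only comparison.

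**5. The comparator texts**

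The Abstract supplies controls with cookware; {12} leaves them with their own. Both cannot be true. The wording in {24b} fits either reading and does not decide it.

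**The case against.** The strongest reply is that the trial's question is the package almost everywhere else. The title joins iron pots and BCC. The Abstract, Trial design {12}, Study setting {13}, the BCC section and part of the Discussion do the same. Testing a bundled intervention against standard care is a legitimate pragmatic design. This stands: the randomised contrast is valid for that question, and the defect lies in Objectives 1 and 2 and in particular Discussion sentences. But objectives define what the trial is meant to answer, and these depart from the design.

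It can also be said that the trial measures diet by 24-hour recall and food frequency questionnaire, and has a nutrition knowledge and practice score. These can show whether diet changed, but not how much of the effect came from pots.

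A reader might infer that controls have no contact with the study team. The article does not establish this: {15c}, the harms ascertainment section and {25b} mention monthly visits without naming an arm. Only the group sessions are expressly for the intervention group.

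A reader might also take {24b} as a further contradiction on the comparator. It is not, since a control woman's own aluminium or steel utensils are also non-iron cookware.

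Finally, the sentence on existing anaemia measures may mean a comparison with the literature or with current programmes, and the content of standard care is not described. What can be said is that no randomised comparison with such measures is described.

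**Conclusion.** The point holds for the objectives and conclusions as worded. Objectives 1 and 2 and the bioavailability sentence claim a pots-only effect that this design cannot identify; the effect of cookware plus BCC against the control condition can be estimated validly. The stronger inference, that the trial as a whole cannot answer its question, is not supported, because the title and the Abstract Background state the package aim.

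The size of any misattribution cannot be computed from the article. The 20% to 80% range rests on assumed BCC effects of 0.2 to 0.5 g/dL, no pot effect, the article's SD of 1.2 g/dL and 91 evaluable women per arm. It illustrates the ambiguity and does not predict a result.

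The conflict between the Abstract and {12} on what controls receive is real and independent of the first defect. Supplying cookware to controls would not remove the BCC difference. It needs settling before the first allocation.

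**What to change.** (a) Reword Objectives 1 and 2 as the effect of iron cookware plus BCC versus the control condition. In the Discussion, limit the cookware-only statements and conclusions to the package, and delete the claims about bioavailability of leached iron and about comparison with existing anaemia prevention measures. Cost: wording only, and a narrower claim. Randomisation, sample size, outcomes and models are unchanged.

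(b) Reconcile the Abstract (Methods) with Trial design {12}, state one control condition throughout, and word {24b} to match. Cost: wording only if {12} describes what will be done. If cookware will in fact be supplied to controls, {12} must be amended and the control-arm cost in the cost-effectiveness analysis must include it.

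Both changes can go through the route in Protocol amendments {31}, and should be in place before allocation starts; Trial status gives December 2025 for recruitment.
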